### Outcomes

The primary endpoint with respect to the efficacy of passive leg cycle exercise in preserving muscle morphology may be the difference in cross-sectional thickness of the dominant quadriceps muscle from initial to final assessment between groups. Secondary efficacy endpoints may include changes in muscle architecture parameters, such as vastus lateralis fascicle length, PA, muscle thickness, and diaphragm thickness and excursion. We will also assess length of ICU and hospital stay, duration of MV, successful extubation, and incidences of patient death. In addition, septic (requiring vasoactive drugs) and non-septic patients will be compared in terms of primary and secondary outcomes.

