### Patients

This is a single-blind RCT that is going to be conducted by the intensive care and physiotherapy departments at the Hospital de Clínicas de Porto Alegre (HCPA)–Universidade Federal do Rio Grande do Sul (UFRGS). Patients of both genders aged ≥18 years will be recruited from among those admitted to the HCPA ICU and undergoing MV from 24 to 48 h after transfer from the emergency department or wards, no more than 1 week after admission. Exclusion criteria will include neuromuscular diseases causing motor deficits, such as strokes, multiple sclerosis, amyotrophic lateral sclerosis, myasthenia gravis and Guillain-Barré syndrome. Patients will also be excluded in the event of the following: extubation less than 48 h after enrollment on the study; hemodynamic instability (norepinephrine > 0.5 μg/kg/min for arterial blood pressure > 60 mmHg); complications during the protocol such as pneumothorax, deep vein thrombosis or pulmonary embolism; Shilley catheter in the femoral vein; reintubation; delayed weaning (3 failed spontaneous ventilation tests); body mass index (BMI) > 35 kg/m^2^ [2]; or emergence of eschar in the calcaneus area during the protocol.

For sample selection, an assessor is going to conduct a daily search for potential trial participants using the hospital computer system. Then, electronic medical records will be reviewed by patient identification, medical diagnosis, and current medical condition in order to assess patients for eligibility. The next of kin to each eligible patient will be approached for study enrollment. Those who agreed to participate will be asked about the laterality of the patient and will be required to provide written consent.

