### Interventions

Conventional (chest and motor) physical therapy is going to be performed by staff physical therapists who have at least 2 years of experience in the care of critically ill patients. All patients will receive 30-min physical therapy sessions twice daily (morning and afternoon). The protocol consists of passive diagonal movements based on the proprioceptive neuromuscular facilitation (PNF) stretching technique for the upper and lower extremities (two sets of 10 repetitions per set of each diagonal movement bilaterally) and manual bronchial hygiene techniques, such as chest compression-vibrations, resuscitation maneuvers with an Ambu® bag, Ambu, Ballerup, DK), and suction of secretions when necessary.

The intervention group (IG), in addition to conventional physical therapy, is going to undertake passive cycling exercise training for the lower extremities using a bedside cycle ergometer (Flexmotor; Cajumoro, São Paulo, SP, Brazil). For the cycling exercise, patients will be in the supine position with the head of the bed elevated to 30 °. Each patient will perform passive cycling movements at 20 rpm for 20 min once daily, 7 days a week, in the afternoon prior to conventional physical therapy, until extubation or day 7 of the protocol. The protocol will be discontinued if hemodynamic instability occurs (requiring norepinephrine >0.5 μg/kg/min for a mean arterial pressure (MAP) >60 mmHg), systolic blood pressure (SBP) >200 mmHg, heart rate <40 beats/min and persistent peripheral arterial saturation < 88 % or if performing tracheostomy is required.

Before and after each exercise session, the cycle ergometer will be cleaned following the cleaning procedures adopted in the ICU and the criteria established by the hospital infection control committee. Before starting the cycling exercise, all procedures will be briefly explained to the patient regardless of their level of consciousness or sedation. To minimize contact with the device, the heel region is going to be covered with sterile gauze and secured with adhesive tape so that the ankle joint will be close to a 90 ° angle. The passive cycling movements generate alternating extension and flexion of the knee and hip, bilaterally, for 20 consecutive minutes. All procedures will be performed under the supervision of one of the investigators.

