### Statistical analysis

Continuous variables will be expressed as mean and standard deviation or standard error, or as median and interquartile range. Categorical variables will be expressed as absolute and relative frequencies. The Shapiro-Wilk test will be used to test the normality of distribution, and Levene’s test will be used to assess homogeneity of variance for all group comparisons. Student’s *t* test for independent samples will be used to compare means between groups, and the Mann–Whitney test will be used to compare medians between groups. Qualitative data will be analyzed using the chi-square test or Fisher’s exact test when at least 25 % of the cells exhibited the expected frequency <5. To evaluate the intra-group effects, the group and subgroups (septic versus non-septic) in changing muscle parameters, the model of Generalized Estimating Equations (GEE) will be performed with Bonferroni adjustment. Analysis of covariance (ANCOVA) will be used to control for confounding factors such as BMI, duration of protocol and duration of MV. Statistical analysis will be performed using SSPS, version 17.0 (SSPS Inc., Chicago, IL, USA). The level of significance is going to be set at 5 % (*p* ≤ 0.05).

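### Exclusions for early extubation, reintubation and delayed weaning select randomised patients on two listed outcomes, successful extubation and duration of MV

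*Protocol article*

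**What the plan says.** **Outcomes section.** After the primary and secondary muscle endpoints it adds: "We will also assess length of ICU and hospital stay, duration of MV, successful extubation, and incidences of patient death".

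**Patients section.** After the neuromuscular exclusions it continues: "Patients will also be excluded in the event of the following: extubation less than 48 h after enrollment on the study". The same list goes on to "reintubation; delayed weaning (3 failed spontaneous ventilation tests"), among other items. Some of these are baseline characteristics, such as BMI. Others are expressly events arising during the protocol.

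**Randomization section.** The person holding the sequence is telephoned only when the participant is already included and about to start.

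**Interventions section.** The protocol is discontinued for several events, among them "or if performing tracheostomy is required".

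**Statistical analysis section.** The general rule for continuous variables is Student's t "test for independent samples will be used to compare means between groups", and "Mann–Whitney test will be used to compare medians between groups". No test is named for duration of MV or length of stay. The article does not say whether excluded patients stay in any analysis.

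**The concern.** A patient who has to be reintubated is a failure of extubation. A patient extubated within 48 h has a short duration of MV, and one who fails three weaning tests will usually have a long one. The exclusion list takes out all three kinds of patient. If they leave after allocation, the groups compared are no longer those that were randomised, and the selection acts on the variables being compared.

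This is not neutral between arms. The Discussion says that physical training can reduce time on MV and in the ICU, so the authors themselves expect these variables to respond to treatment. If cycling speeds extubation, more cycling patients fall under the 48 h rule and part of the benefit is hidden. If it slows weaning or leads to more reintubation, part of the harm is hidden. Blinding is described for the ultrasound examiner only.

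A second, weaker issue concerns death. A patient who dies on the ventilator has a short duration of MV and a short stay, which look favourable if read as plain numbers.

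**Working it through.** **1. The plan's own figure.** The only computed figure is the sample size, which concerns quadriceps thickness. Inputs from the Sample size calculation section: effect 1.2 (worded as standard errors, read here as SDs), 5% significance (taken as two-sided) and 85% power. Normal approximation: n = 2 × (1.960 + 1.036)² / 1.2² = 12.5, so 13 per group. The exact t calculation gives 14 (power 0.863; 13 gives 0.835). The stated 14 per group reproduces, and nothing below depends on it.

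**2. Timing.** Extubation within 48 h of enrolment can be known only after enrolment. Allocation is released at inclusion, when the protocol is about to start, so this exclusion normally falls after randomisation. Reintubation and delayed weaning carry no time qualifier. Patients enter after only 24 to 48 h of MV, when three failed weaning tests are unlikely, and neighbouring items are tied to the period after enrolment. Both therefore read most naturally as later events.

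**3. Successful extubation.** Suppose success means extubated and not reintubated. Let E patients in an arm be extubated and r of them reintubated.
- All extubated patients: success = (E − r)/E.
- After reintubated patients are excluded: (E − r)/(E − r) = 100%, whatever r is.

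The 100% needs that definition and an extubated-only denominator. With all retained patients as denominator, deaths and patients still ventilated remain as failures.

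**4. Illustration with assumed inputs** (none is in the documents). Time to extubation is lognormal with log-SD 0.7 and median 6 days (control) or 4.5 days (cycling). Reintubation is 15% versus 8%. Delayed weaning is about 20% versus 10%, rising with time on MV. The death hazard on MV is constant and equal in both arms. The three exclusions are then applied.

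| Death hazard per day | Success, all randomised (control vs cycling) | Success, after exclusions | Mean MV difference, all randomised | Mean MV difference, after exclusions |
|---|---|---|---|---|
| 0 | 85% vs 92% | 100% vs 100% | 7.66 − 5.75 = 1.9 d | 7.35 − 6.13 = 1.2 d |
| 0.02 | 73% vs 82% | 80% vs 86% | 6.82 − 5.26 = 1.6 d | 6.57 − 5.57 = 1.0 d |
| 0.05 | 60% vs 71% | 61% vs 70% | 5.86 − 4.67 = 1.2 d | 5.66 − 4.90 = 0.8 d |

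The exclusions remove between 22% and 35% of an arm. The MV difference shrinks by about a third (with no deaths, 1.22/1.91 = 0.64). The loss in the extubation contrast is largest when few patients die. These runs assume that cycling helps, so they show attenuation. Other assumptions would move the result the other way.

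**5. Deaths.** With identical times to extubation, raising the assumed death hazard from 0.02 to 0.06 per day lowers the observed median MV from 5.4 to 4.5 days before any exclusion. In a small example of 14 per arm, deaths occur on day 3 (4 versus 2) and all survivors have 8 days. The means are (4×3 + 10×8)/14 = 6.57 and (2×3 + 12×8)/14 = 7.29, a difference of 0.71 day. The medians are 8 and 8, and Mann–Whitney and t test both give p = 0.38. The distortion appears in the means but not in the medians.

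**The case against.** **Excluded may mean only that the protocol stops.** The norepinephrine threshold appears both as an exclusion and as a reason to discontinue the protocol, and the exclusion list mixes baseline items with later events. Reintubation could describe a patient at screening. This stands as a real ambiguity. It does not remove the problem, because the 48 h rule can apply only after enrolment and nothing says that such patients remain in the analysis.

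**A reader might infer that these outcomes become uninformative, or that success is 100% in both arms.** The article does not support that. It defines neither success nor its denominator, and in the illustration two thirds of the MV difference survives. Length of stay is not itself an exclusion criterion.

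**A reader might also infer that a t or Mann–Whitney comparison flawed by death is fixed for MV duration and stay.** It is not: the Statistical analysis section gives a general rule and does not name these variables. Handling of deaths may sit in the full protocol or analysis plan, and death is listed as an outcome, so an imbalance would be visible. The death issue is therefore a caution about interpretation, not an error in the plan.

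**The stakes are limited.** These are additional outcomes in a 28-patient trial sized for quadriceps thickness. That lowers the weight of the point but does not answer it.

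**Conclusion.** The point holds in a limited form. The stated exclusions, certainly the 48 h rule and on the natural reading the other two, select randomised patients on successful extubation and duration of MV. The comparison of these outcomes is truncated and can be biased in either direction. The size cannot be given, because the documents contain no rates of early extubation, reintubation, delayed weaning or death. Under the assumed rates above, a 7-point difference in extubation success vanishes when nobody dies, and the MV difference falls by about a third.

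The conclusion rests on excluded meaning removed from the analysis, which the text suggests but does not say. This is not a matter left to a later analysis plan, since such a plan would have to override or reinterpret a stated rule. The primary sample size is not challenged here. The point should be settled before analysis, but it does not bear on the primary endpoint as argued here.

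**What to change.** 1. State in the Patients section which listed events are screening criteria and which are later events. State that, whatever the later events mean for the study intervention (a clinical matter on which no view is taken here), they do not remove a randomised patient from the analysis of successful extubation, duration of MV, length of stay and death.
2. Analyse these outcomes in all randomised patients as allocated.
3. Define successful extubation. Count reintubation, or death or no extubation by the end of follow-up, as not successfully extubated. Classify delayed-weaning and tracheostomy patients by their eventual result. Calling every delayed-weaning patient a failure would misclassify those later extubated.
4. Report deaths by arm beside duration of MV and stay, and do not read shorter raw durations as benefit without them. A ranking with deaths worst, such as ventilator-free days, is an optional sensitivity analysis that the documents do not require. Its horizon would have to be chosen, since the article gives none.

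**Cost.** Wording, plus a little extra record review for patients who would otherwise have been dropped. The article describes electronic records for screening only, so their completeness for later follow-up should be confirmed. Durations will be more heterogeneous.

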### Sample size calculation

The sample size calculation is based on a pilot study with 10 patients. To achieve an effect size of 1.2 standard errors between groups as cross-sectional thickness of the quadriceps muscle, significance level of 5 % and power of 85 % and 2 repeated measures (initial and final), the sample size estimated by the (WinPepi, http://www.brixtonhealth.com/pepi4windows.html) 11.43 statistical program was of 14 patients in each group.

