**Methods/Design:**

A single-blind randomized controlled trial (the MoVe ICU study) will be conducted to evaluate and compare the effects of early rehabilitation using a bedside cycle ergometer with conventional physical therapy on the muscle morphology of the knee extensors and diaphragm in critical ill patients receiving MV. A total of 28 adult patients will be recruited for this study from among those admitted to the intensive care department at the Hospital de Clínicas de Porto Alegre. Eligible patients will be treated with MV from a period of 24 to 48 h, will have spent maximum of 1 week in hospital and will not exhibit any characteristics restricting lower extremity mobility. These subjects will be randomized to receive either conventional physiotherapy or conventional physiotherapy with an additional cycle ergometer intervention. The intervention will be administered passively for 20 min, at 20 revolutions per minute (rpm), once per day, 7 days a week, throughout the time the patients remain on MV. Outcomes will be cross-sectional quadriceps thickness, length of fascicle, pennation angle of fascicles, thickness of vastus lateralis muscle, diaphragm thickness and excursion of critical ICU patients on MV measured with ultrasound.

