### Randomization

Patients will be randomly assigned to receive either conventional physical therapy (conventional group) or exercise training intervention using a cycle ergometer associated with conventional physical therapy (intervention group). Randomization sequence is going to be created by using the website www.randomization.com, with a 1:1 allocation ratio using blocks of 10 participants.

To ensure the confidentiality of randomization sequence, the sequence will be generated by an assessor who has not participated in data collection or study design and will be contacted by telephone only after the participant has been included in the study and is ready to start the protocol.

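### The effect size of 1.2 standard errors does not give 85% power with 14 per group; 1.2 standard deviations does, and only if all 28 recruited patients are evaluable

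*Protocol article*

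**What the plan says.** The Sample size calculation section of the protocol article takes its inputs from a pilot: "The sample size calculation is based on a pilot study with 10 patients". The target is given as "To achieve an effect size of 1.2 standard errors between groups as cross-sectional thickness of the quadriceps muscle", with "significance level of 5 % and power of 85 % and 2 repeated measures (initial and final") as the other inputs. The result from the "statistical program was of 14 patients in each group". No raw difference, SD, within-patient correlation or sidedness is given.

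The Abstract states: "A total of 28 adult patients will be recruited for this study". Allocation is 1:1.

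The Outcomes section makes the primary endpoint the change in quadriceps thickness between the two scans, compared between groups. The Statistical analysis section plans an independent-samples t test for means.

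The Patients section lists exclusions that can arise only once a patient is in the study: "Patients will also be excluded in the event of the following: extubation less than" 48 h after enrolment, complications during the protocol, and a heel lesion appearing during the protocol. Reintubation and delayed weaning are on the same list. Death is among the outcomes. The article gives no rate for any of these and does not say whether excluded patients are replaced.

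**The concern.** An effect size for a two-group comparison of means is normally expressed in SDs. A standard error depends on the sample size, so an effect stated in standard errors has no fixed meaning until one knows which SE is meant and at what n. If it is the SE of the difference being tested, an effect of 1.2 lies below the critical value of about 2.06 (t, 26 df), and high power is impossible.

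This sentence is the only justification given for the trial's size. If the unit is wrong, the target difference cannot be reconstructed, and a null result would be judged against an 85% power that the stated inputs do not support. Separately, recruiting exactly the number the formula returns leaves no margin when the plan removes patients after enrolment.

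**Working it through.** **Inputs.** From the article: effect 1.2, alpha 5%, power 85%, 14 per group, 1:1 allocation, t test, pilot of 10. Assumed: a two-sided test, and a 5+5 pilot split where a pilot group size is needed.

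**Method.** With standardised effect d and n per group, the noncentrality is d × √(n/2) on 2n − 2 degrees of freedom. Power comes from the noncentral t distribution.

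**1. Reproducing the stated 14, reading the unit as SD (d = 1.2).**
- Normal approximation: 2 × (1.960 + 1.036)² / 1.2² = 12.47, so 13 per group.
- Noncentral t at n = 13: noncentrality 1.2 × √6.5 = 3.06, power 83.5%.
- Noncentral t at n = 14: noncentrality 1.2 × √7 = 3.17, power 86.3%.

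The smallest n that reaches 85% is 14, which is the article's figure.

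**2. Taking the words literally (1.2 SE), at 14 per group.** Here the SE is that of the quantity analysed.

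| Whose SE | d in SD units | Power | n per group for 85% |
|---|---|---|---|
| Between-group difference, this trial | 1.2 × √(2/14) = 0.454 | 21.2% | 89 |
| Mean of one group of 14 | 1.2/√14 = 0.321 | 12.9% | 176 |
| Mean of 10 pilot patients | 1.2/√10 = 0.379 | 16.2% | 126 |
| Mean of 5 pilot patients | 1.2/√5 = 0.537 | 27.7% | 64 |
| Difference in a 5+5 pilot | 1.2 × √(2/5) = 0.759 | 49.0% | 33 |

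None gives 85%. A one-sided 5% test does not rescue them: the highest value becomes 62%.

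**3. Which SD?** If 1.2 is in SDs of raw thickness and rho is the initial-final correlation, the change score has variance 2(1 − rho) times the raw variance. So d for change is 1.2/√(2(1 − rho)).

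| rho | d for change | Power at 14 per group | n per group for 85% |
|---|---|---|---|
| 0 | 0.849 | 58% | 26 |
| 0.3 | 1.014 | 73% | 19 |
| 0.5 | 1.200 | 86% | 14 |
| 0.7 | 1.549 | 98% | 9 |

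The stated 14 therefore fits 1.2 SD of change, or 1.2 SD of raw thickness with rho = 0.5, but not the other correlations shown.

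**4. Margin for loss.** 2 × 14 = 28, the number to be recruited. For d = 1.2:

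| Evaluable per arm | Power |
|---|---|
| 14 | 86.3% |
| 13 | 83.5% |
| 12 | 80.2% |
| 11 | 76.3% |
| 10 | 71.8% |

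The effect detectable with 85% power is 1.18 SD at 14 per arm, 1.28 at 12 and 1.42 at 10. These rows show a range; the article gives no loss rate from which to forecast one.

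**The case against.** The strongest reply is that this is a slip of one word. The calculation reproduces exactly with deviations in place of errors, so the program was very probably run on the right scale, and neither the sample size nor the analysis changes. That stands. It means that 21% is the power implied by the printed words, and is not a fair description of the trial.

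A reader might go further and infer that power is 21% at most. The article does not support that bound. It bases the calculation on a pilot, and SEs from the pilot give up to 49%. One could also suppose an SE of raw thickness combined with a high correlation. Reaching d = 1.18 for change would need 2(1 − rho) = (0.454/1.18)² = 0.148, so rho of about 0.93, with this trial's SE of the difference. With a 5+5 pilot it would need (0.759/1.18)² = 0.414, so rho of about 0.79. The article states no correlation, so such a reading can be constructed but not checked.

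A second tempting inference is that naming two repeated measures while arriving at the plain two-sample n is itself an error. It is not: at rho = 0.5 a change score has the same variance as a single measurement, and an SD of change already contains both scans. Pilot means and the correlation are also details that an article may leave to the full protocol. What remains is that the unit is stated wrongly, and correcting it leaves open which SD is meant.

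A third is that the plan's own exclusions rule out 28 evaluable patients. The list mixes conditions that can be screened at entry with later events, gives no frequencies, and is silent on replacement. Losing one patient per arm leaves 83.5%. Only the weaker statement holds: without replacement, 28 evaluable patients is unlikely.

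**Conclusion.** The point holds as a wrong unit in the figure that justifies the trial's size. As printed, the assumption gives 13% to 49% power at 14 per group across the SE readings tried, against the stated 85%. Read as 1.2 SD it gives 86.3%, and the stated 14 is correct, provided that the SD is that of the change score or that the correlation behind a raw SD is 0.5. If the SD is of raw thickness and the correlation is different, power for the change in thickness could lie between 58% (correlation 0) and 98% (correlation 0.7).

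The attrition point is secondary. The 85% belongs to 28 evaluable patients, and 28 is also the number to be recruited. Without replacement, some shortfall is likely; its size cannot be derived from the article.

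All of this assumes a two-sided 5% test. The documents do not show that the trial is planned at 21% power, nor that its target power is unattainable.

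**What to change.** In the Sample size calculation section:

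1. Replace standard errors with standard deviations, after checking against the inputs given to the program.
2. Say whether the SD is of the change or of thickness, give the initial-final correlation used, and give the pilot difference and SD in mm. State that the test is two-sided, if that is so.
3. State that 85% refers to 28 evaluable patients, and say whether patients excluded after enrolment are replaced.
4. Restate the power, or the detectable effect, at the evaluable number expected after exclusions and deaths before the second scan.

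This is a text correction with no added enrolment and no change to the analysis. Its cost is that the stated power will look less favourable if fewer than 28 patients are expected to be evaluable.
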